## Abstract

**Background:**

Many patients with COVID-19 present the so-called post-acute sequelae of COVID-19 such as fatigue, post-stress discomfort, dyspnea, headache, pain mental impairment, incapacity to perform daily physical tasks ant exercise intolerance. This study aims to investigate the effects of different exercise programs on physical and mental fitness, physical condition and biomarkers of the immune system and oxidative stress in older patients with post-COVID-19 sequelae.

**Methods:**

The sample will be made up of 120 eligible participants, over the age of 60 years who have had COVID-19 disease and are survivors and present persistent COVID-19 symptomatology diagnosed by the corresponding physician. The participants will be randomly assigned to the experimental groups: supervised endurance group (SEG, *n* = 30), supervised strength group (SSG, *n* = 30), supervised concurrent group (SCG, *n* = 30), which will perform the corresponding exercise program 3 days a week compared to the control group (CG, *n* = 30), which will not carry out a supervised exercise program. The design of this project will include measurements of four relevant dimensions; 1) Cardiorespiratory fitness; 2) Muscle fitness; 3) Pain and mental health; and 4) Biomarkers of inflammation and oxidative stress.

**Conclusions:**

The results of this study will provide insights into the effects of different exercise programs on physical and mental fitness, physical condition and biomarkers of the immune system and oxidative stress in older patients with post-COVID-19 sequelae. These findings may be the basis for the formulation of health plans and rehabilitation programs that allow healthy aging and a reduction in the associated morbidity in patients with post-COVID-19 sequelae.

**Trial registration:**

NCT05848518. Registered on May 8, 2023.

**Supplementary Information:**

The online version contains supplementary material available at 10.1186/s12877-023-04544-3.

## Introduction

Coronavirus 2019 disease (COVID-19) was first identified in Wuhan, Hubei, China in December 2019 and is caused by the severe acute respiratory syndrome coronavirus 2 (SARS-CoV-2) [1]. The disease spread very rapidly to the rest of China and then throughout the world. In Spain, a state of alarm was declared on March 16, 2020 with the aim of managing the health care emergency produced by COVID-19. By August 9, 2022, 13,280,557 confirmed cases of COVID-19 and 111,339 deaths had been registered in Spain (https://www.sanidad.gob.es/profesionales/saludPublica/ccayes/alertasActual/nCov/documentos/Actualizacion_623_COVID-19.pdf). More than 100 million persons worldwide have been affected, with a hospitalization rate of 4.6 per 100,000 inhabitants. Fortunately, most of these patients remain alive [2, 3].

However, many patients with COVID-19 present the so-called post-acute sequelae of COVID-19. Between 10 and 20% of the patients with severe COVID-19 symptoms evolved with a phase of persistence of clinical manifestations such as fatigue, post-stress discomfort, dyspnea, headache, pain and many other neurocognitive conditions described such as mental impairment, and incapacity to perform daily physical tasks [4]. In addition, many patients present muscle weakness, intolerance to exercise [5] and a greater probability of developing stress, irritability, insomnia, confusion or frustration [6].

Consequently, many of these survivors of COVID-19 cannot perform their normal activities 60 days after hospital discharge [7], and approximately 60% of hospitalized patients present dyspnea, fatigue and muscle weakness as post-COVID-19 sequelae up to 7 months after hospitalization [8–10]. These post COVID-19 sequelae seem to be more evident in older persons with associated comorbidities, rapidly diminishing their quality of life [11] and, what is worse, increasing the risk of death in the older people compared with other age groups [12–14].

From a biological perspective, older people have shown to be more vulnerable to COVID-19, increasing the imbalance between reactive oxygen species and the mechanisms of antioxidant defense, exacerbating oxidative stress [15]. The dysregulation of immune function related to age can cause a more overt pathophysiological response to SARS-CoV-2 infection in older patients, which can accelerate the risk of biological aging, increasing oxidative stress, even after post-COVID-19 recovery [16].

Up to now, many pharmacological therapies have been used but few have demonstrated true effectiveness in post-COVID-19 survival and none, to date, has shown to reduce the sequelae of the disease, or specifically, the evolution of persistent symptoms even with global vaccination of the population [17].

There is overwhelming evidence that exercise produces benefits for health in the short, medium and long term, which prevents, delays, mitigates and even reverses many metabolic, pulmonary, cardiovascular, neurocognitive, inflammatory, rheumatic and musculoskeletal diseases, reducing fatigue and pain, increasing tolerance to exercise and daily life activities [18–23], and improving physical and mental health [24].

Although the need for effective scientific evidence-based exercise and rehabilitation programs in the period following COVID-19 is clear, the volume of patients requiring support and care will generate an unprecedented demand for medical care services worldwide. There are few studies on the benefits of exercise in the post-COVID-19 syndrome in older people. The last recommendations emphasize the need for physical activity adjusted to the symptoms and personalized exercise in post-COVID-19 recovery [25], with the aim of helping patients with post-COVID-19 sequelae achieve rapid recovery, improve their autonomy and, consequently, quality of life, especially in older persons.

Given the numbers of survivors suffering these post-COVID-19 sequelae, it is not only incentivizing but it is essential to produce knowledge to determine exercise schedules that are the most recommendable for improving the symptoms of the post-COVID-19 syndrome in relation to cardiorespiratory and muscular fitness (fatigue, muscle weakness), pain, mental health and biomarkers of inflammation and oxidative stress, taking into account the differences between older males and females.

### General, specific, transversal, partial and final objectives

#### General objective (GO)

Study the effects of different exercise programs on physical and mental fitness, physical condition and biomarkers of the immune system and oxidative stress in older patients with post-COVID-19 sequelae.

#### Specific objectives (SO)

Evaluate the effectiveness of different exercise programs in older patients with post-COVID-19 sequelae in relation to:

SO1. Muscle fitness; SO2. Cardiorespiratory fitness; SO3. Pain; SO4. Mental health; SO5. Biomarkers of the immune system; SO6. Biomarkers of oxidative stress.

#### Transversal objectives (TO)

TO1. Consider the perspective of sex and gender in all the SO.

#### Partial objectives (PO)

The partial objectives are designed according to the temporal needs of achieving the SO.

PO1. Recruit and select older patients with post-COVID-19 sequelae; PO2. Elaborate and supervise the exercise program according to the schedules established by the Department of Sports Medicine and Rehabilitation of the Hospital of Mataró; PO3. Perform evaluations of cardiorespiratory and muscle fitness, pain and mental health, and biomarkers of inflammation and oxidative stress prior to the initiation of the exercise program in older patients with post-COVID-19 sequelae; PO4. Collect the data and develop the database of the evaluations prior to the initiation of the exercise program; PO5. Implement the different exercise programs in older patients with post-COVID-19 sequelae; PO6. Perform the evaluations of cardiorespiratory and muscle fitness, pain and mental health and biomarkers of inflammation and oxidative stress in older patients with post-COVID-19 sequelae after completing the exercise program; PO7. Collect the data and develop the database of the final evaluations after the exercise program; PO8. Analyze and interpret the data.

#### Final objectives (FO)

FO1. Elaborate the corresponding reports; FO2. Report the knowledge generated to different informative media such as congresses, research meetings, scientific journals with impact, the media, etc.; FO3. Report and transfer knowledge of the results of the project to society: talks, activities in civic centers or centers for the older people.

## Methods

### Study design

The study design is shown in Fig. 1. This project will carry out a randomized controlled trial to determine what type of supervised exercise program is the most effective compared with a control group: supervised endurance group (SEG), supervised strength group (SSG), supervised concurrent group (strength and endurance) (SCG) and control group (CG). The Clinical Trials Registry is NCT05848518 (Last Update Posted: May 08, 2023). The protocol of study will be developed according to the Recommendations for Interventional Trials (SPIRIT) guidelines (Additional file 1) for randomized controlled trials [26].

**Fig. 1 Fig1:**
[figure not shown]
Study design. Abbreviations: CG = unsupervised control group; EG = experimental group; RANDO = randomization; SCG = supervised concurrent group; SEG = supervised endurance group; SEG = supervised strength group

The project will be divided into 3 subprojects and performed in coordination by three institutions as follows:i)Subproject of the consolidated research group on pain, physical activity, nutrition and health (Acronym: DAFNiS) of the *Campus Docent Sant Joan de Déu. Universitat de Barcelona, Spain*. “Effects of a physical exercise program (aerobic, strength or combined/concurrent) on muscle fitness, pain and mental health in older patients with post-COVID-19 sequelae”.ii)Subproject of the *Hospital de Mataró-Barcelona, Spain*: “Evaluation of cardiorespiratory and muscular fitness in older patients with post-COVID-19 sequelae”.iii)Subproject of the *Departamento de Fisiología e Inmunología. Universidad de Barcelona, Spain*. “Evaluation of biomarkers of inflammation and oxidative stress in older patients with post-COVID-19 sequelae”.

### Participants and criteria of eligibility

The sample will be made up of 120 eligible participants, over the age of 60 years who have had COVID-19 disease and present persistent COVID-19 symptomatology with sequelae of fatigue, muscle weakness, pain, difficulty in performing daily life activities, etc. diagnosed by the corresponding physician.

Participants will be recruited from internal medicine services and patients with post-COVID-19 sequelae will be selected from the database of the hospital and primary care centers who have given their consent to be contacted for participation in the research project. The recruitment status of the participants will be ongoing at the time of manuscript submission.

Candidates will fulfill the following inclusion criteria:Persons of both sexes (and different expression of gender) older than 60 years of age.Molecular diagnosis (reverse transcription polymerase chain reaction [RT-PCR]) of infection by SARS-CoV-2.No history of physical diseases and no disease or disability that limits participation in the exercise program or precludes the corresponding measurement/evaluations.Be able to communicate without difficulty.Be able to understand the objectives of the project and provide written, informed consent.Not taking any medication that can affect normal performance of the exercise program and the evaluations. Specifically, patients who were treated with IL-6 receptor antagonists (example: tocilizumab) during the last month will be excluded. This type of medications will interfere with the exercise adaptations of the cardiorespiratory system.

The following exclusion criteria will apply:Having acute or terminal disease or any other disease that may affect the normal practice of a supervised exercise program and the corresponding evaluations.Consumption of any amount of alcohol or drugs during the study.Be performing any type of activity that may interfere in carrying out the supervised exercise program or the evaluations.Not completing the study once initiated or wishing to participate in the control group.

To calculate the sample size of this project a type 1 (α) error of 5% and a 95% confidence interval with a level of precision (d = 0.095) was established for the test of proportional hypotheses resulting in a sample size of *n* = 108 persons, increased by 10% (rounded up to *n* = 120) to compensate for possible dropouts along the study period.

To know the sample size more precisely in the hypothesis test of means it will be necessary to carry out a pilot study which will provide the size of effect and statistical power (0.80), determine the analysis to perform, obtain delta values in the units corresponding to the principal study variable as well as know the standard deviation. Since this cannot be carried out, the sample size described in the study by Udina and cols. (2021) [27] will be used, which established a slightly lower sample size (Total *n* = 33, subgroups of *n* = 20 and *n* = 13). Therefore, it is assumed that the theoretical sample calculation can be considered as correct given the above.

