### Randomization, allocation concealment, and blinding

The eligible participants will be randomly assigned to the groups: SEG (*n* = 30), SSG (*n* = 30), SCG (*n* = 30), which will perform the corresponding exercise program 3 days a week compared to the CG (*n* = 30), which will not carry out a supervised exercise program. The method to generate the 1:1 allocation sequence to one of 4 experimental groups will be computer-generated random numbers (Research Randomizer). The assignment will be made using previously constructed balanced blocks until a total of 120 participants are assigned with the same number of participants per experimental group.

All participant assignment keys will be saved in a confidential file in the Campus Docent Sant Joan de Déu. An alphanumeric code will be assigned to each experimental group to guarantee masking. Once this process is completed, participants will be assigned to the corresponding experimental group. The alphanumeric code will be known by one of the researchers and will not be disclosed to the rest of the researchers until the analysis of the interventions is completed. Due to the characteristics of the intervention process in each experimental group, participants cannot be blinded to the exercise training programs. However, researchers and collaborators will be blinded to participant data during the baseline, intervention, and assessment processes. Blinding will be performed for all data.

The design of this project will include measurements of four relevant dimensions (Fig. 1): 1) Cardiorespiratory fitness; 2) Muscle fitness; 3) Pain and mental health; and 4) Biomarkers of inflammation and oxidative stress. In all cases, differences which may derive from variables of sex and gender will be considered.

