### Data collection, management and analysis

An instruction manual for data collection and patient follow-up along the intervention process will be created. This manual will include the methodology of data collection and a detailed description of all the instruments used to obtain the study data. An initial protocol will be used for data entry, which will include specifications aimed at minimizing coding errors. All the technical personnel involved will undergo training sessions on the field work to harmonize data collection. Standardized protocols for quality control and data filtration will be developed. A centralized database will be designed for the data of the different participating centers. A central analytical plan will be developed, and the group coordinator of the project (*Campus Docent Sant Joan de Déu*) will provide data analysis and reports of study data in an agreed format. Only the principal investigator and the expert in research methodology and statistics will have information on the trial data until the end of the trial. Only anonymized data of the participants will be recorded.

An expert in research methodology and statistics will be in charge of designing the methodological focus and the statistical techniques that will be used to analyze the data obtained of each variable. Briefly, descriptive statistics will be calculated for the overall sample and between the experimental groups taking into consideration the gender perspective. Subsequently, the corresponding parametric or non-parametric analyzes will be carried out to establish the minimum intra- and inter-group changes of the variables analyzed. Missing cases will continue in the final analysis, however, they will provide less information and decrease the variance of the estimated effects to a lesser extent than the existing cases at each assessment stage.

An α value ≤ 0.05 will be considered to indicate statistical significance. The final analysis of the study will be fully described and differences between the enrolled experimental groups will be presented to determine the effectiveness of the exercise programs.

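### Non-completion is listed as an exclusion criterion although it can only be known after randomisation, and this conflicts with the statement that missing cases stay in the final analysis

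*Protocol article*

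**What the plan says.** In the Protocol article, *Participants and criteria of eligibility*, the list opens with "The following exclusion criteria will apply". Two of its items refer to the period after a participant has started:

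- "Not completing the study once initiated or wishing to participate in the control group"
- "Consumption of any amount of alcohol or drugs during the study"

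*Randomization, allocation concealment, and blinding* then states "The eligible participants will be randomly assigned to the groups", so eligibility is meant to be settled before assignment.

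*Data collection, management and analysis* gives the only rule shown for incomplete participants: "Missing cases will continue in the final analysis, however, they will provide less information".

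The sample size of 108 is "increased by 10% (rounded up to *n* = 120) to compensate for possible dropouts along the study period". *Limitations* repeats the 10% figure, allows that dropout may be higher, and names illness, lack of motivation and post-COVID symptoms among the reasons for leaving. *Process of evaluation* has two assessments, before the programme and at 12 weeks.

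**The concern.** An exclusion criterion decides who belongs in the trial. If it depends on what happens after assignment, the groups being compared are no longer those formed by randomisation. Someone who stops before week 12 and has no final evaluation is excluded under the eligibility section and is a retained missing case under the analysis section. The document does not say which rule governs, and it does not separate eligibility from withdrawal or from membership of the analysis.

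The people affected are unlikely to be a random subset. The stated reasons for leaving are close to the outcomes being measured (fitness, pain, mental health). The arms also ask different things of participants: three supervised sessions a week in the exercise arms, against usual habits and a weekly telephone call in the control group. Dropout linked to both arm and outcome would bias a completers-only comparison, and further recruitment would restore the numbers without removing that bias. If the choice between the two rules is left until results are visible, the analysis population becomes a data-dependent decision.

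**Working it through.** **1. The texts side by side.**

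| Question | Eligibility section | Analysis section |
|---|---|---|
| Participant stops and has no 12-week evaluation | Meets an exclusion criterion | Stays in the final analysis, contributing less information |
| Participant uses alcohol or drugs on study but attends week 12 | Meets an exclusion criterion as worded | Not addressed, since data are complete |

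The first row is a conflict. The second is a timing problem in the wording only.

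**2. The plan's own figures.** Inputs from the eligibility section are a 5% type 1 error, a 95% interval, d = 0.095 and 10% dropout. The proportion is not stated, so p = 0.5 is assumed.

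- n = 1.96² × 0.5 × 0.5 / 0.095² = 106.4, rounded up to 107, against the stated 108.
- 108 / 0.90 = 120, as stated (108 × 1.10 = 118.8, or 119, rounded up to 120).

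The figures reproduce closely and are not in dispute.

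**3. How many people the rule touches.** At 10% dropout, 0.10 × 120 = 12 randomised participants, leaving 108, or 27 of 30 per arm if losses are even.

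**4. Loss of precision (a minor part).** The detectable standardised difference between two arms at 80% power and two-sided 5% is (1.960 + 0.842) × √(2/n).

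- n = 30: 0.72 SD
- n = 27: 0.76 SD

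**5. Possible selection bias (illustration only).** Completer mean minus full-arm mean = dropout proportion × (completer mean minus dropout mean). Assume that those who stop would have been 0.5 to 1.0 SD worse than completers. The splits by arm are also assumed.

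| Dropout, exercise arm | Dropout, control | Net bias (positive favours exercise) |
|---|---|---|
| 20% | 5% | (0.20 − 0.05) × 0.5 to 1.0 = +0.075 to +0.15 SD |
| 10% | 10% | 0 |
| 5% | 20% | −0.075 to −0.15 SD |

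A second route assumes no true effect, normal outcomes and outcome-related dropout in one arm only. If the poorest outcomes are exactly those lost, that arm's completer mean shifts by φ(z_d)/(1 − d), where d is the dropout proportion and z_d its normal quantile. This gives 0.19, 0.35 and 0.50 SD at 10%, 20% and 30% dropout. With an assumed correlation of 0.3 between dropout tendency and outcome, the shifts are 0.06, 0.10 and 0.15 SD. The sign depends on which arm loses people.

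**The case against.** The strongest reply is that the eligibility section never says excluded people leave the analysis. The only sentence on analysing incomplete cases keeps them, so a non-completer could be out of the programme while the data already collected stay in. The non-completion item also shares its line with a preference about the control group, which is an attitude at screening, so the authors may have meant unwillingness to commit. This stands in part: a reader might infer that the protocol prescribes a completers-only analysis, and it does not say so. It does not rescue the text, because stopping once started has no literal screening meaning and removal is the natural effect of an exclusion criterion.

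Three further objections stand:

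- **Alcohol and drugs.** A reader might infer that this criterion also contradicts the missing-cases statement. It does not, since such a participant may have complete data, and the item can be read as a commitment to abstain made at screening. The documents give no rate of use, so no number of affected participants can be given.
- **Direction of bias.** A reader might infer that the exercise arms are flattered. The protocol gives one pooled dropout rate and nothing by arm, and the table in the working shows that the sign can reverse or vanish.
- **Source of bias.** With a single assessment after baseline, a dropout without a week-12 value adds little. Deleting the wording alone would leave much of the same selection in place.

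It is also fair that formal definitions of analysis populations are commonly left to an analysis plan, and their absence is not the point here. The point is two statements in the same document that pull in opposite directions.

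**Conclusion.** The concern holds for non-completion. It is listed as an exclusion, can be known only after randomisation, and conflicts with the statement that missing cases remain in the final analysis. On the protocol's own 10% dropout it concerns 12 of 120 randomised participants, and more if dropout exceeds the estimate, which the protocol regards as possible.

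A completers-only comparison could be biased because the expected reasons for leaving are plausibly related to outcome and may differ by arm. The SD figures in the working are illustrations resting on assumed dropout splits and outcome gaps. They are not estimates for this trial, and the conclusion does not depend on them.

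The alcohol and drug item is a secondary wording point about when the criterion is judged.

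**What to change.** - Delete non-completion from the exclusion criteria and treat it as discontinuation.
- State that eligibility criteria apply only to facts known before randomisation.
- State that the already planned 12-week evaluation is sought from every randomised participant regardless of attendance. Without this step the deletion recovers little.
- State that all randomised participants are analysed in their assigned arm, in line with the existing sentence on missing cases.
- Clarify that the alcohol and drug criterion is judged at screening, and that on-study use does not remove a randomised participant from the analysis.

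The cost is a short text correction, some effort to bring non-attenders to a visit that already exists, and possibly a smaller effect estimate. No sample-size figure changes. Recruitment was described as ongoing at submission, so the correction should be made and dated before outcome data are seen by group.

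### The target of 120 comes from a precision calculation for a proportion, supports none of the planned between-arm comparisons, and is declared correct by appeal to a study of 33

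*Protocol article*

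**What the plan says.** The sample-size text closes the protocol article's section on participants and eligibility. It sets "a type 1 (α) error of 5% and a 95% confidence interval" as its error and confidence levels. The basis for the number is then worded "with a level of precision (d = 0.095) was established for the test of proportional hypotheses resulting in a sample size of", and the figure that follows is 108. The allowance for dropout stands in the same sentence: "resulting in a sample size of *n* = 108 persons, increased by 10% (rounded up to *n* = 120) to compensate for possible dropouts". No power, between-group difference, expected proportion or number of groups enters the calculation.

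The next paragraph says that sizing a test of means would need a pilot study to supply the effect size, power of 0.80, delta and standard deviation, and that no pilot can be run. It turns instead to a cited study, "which established a slightly lower sample size" (33 in total, in subgroups of 20 and 13), and concludes: "it is assumed that the theoretical sample calculation can be considered as correct given the above".

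The Study design section gives the aim as to "determine what type of supervised exercise program is the most effective compared with a control group". The randomization section allocates 30 participants to each of four arms. The primary outcomes are distances, repetition counts, times, strength, flexibility and balance measures, and biomarker levels. The analysis section plans within-group and between-group comparisons of change.

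**The concern.** The calculation answers a different question from the one the trial asks. Precision for a proportion fixes how closely a percentage is estimated. It says nothing about the chance of detecting a difference in mean walking distance, strength or a biomarker between two arms. The article sees the gap and then closes it with a comparison that cannot close it: another study's smaller enrolment does not show that this size suits a four-arm comparison.

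Two things are at stake. Readers are told that the size has been checked when no calculation for the planned comparisons exists. And the Limitations section uses the estimated sample as the trigger for a second recruitment phase, for redistributing groups and admitting participants aged 50 to 60, and finally for reducing the trial to two arms. A number with no stated link to the trial's question therefore governs changes to its design.

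**Working it through.** **Inputs from the article.** Alpha 0.05 with a 95% interval (so two-sided); precision d = 0.095; 108 before and 120 after dropout; 10% dropout; four equal arms of 30; cited study of 33 (20 and 13).

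**Assumed, because not stated.** Proportion p = 0.5; standardised effects (SD = 1); pre-post correlation r = 0.7, range 0.5 to 0.8.

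**1. Reproducing 108 and 120.** The precision formula for one proportion is n = z² × p(1 − p) / d².
- 1.96² × 0.25 / 0.095² = 0.9604 / 0.009025 = 106.4, so 107.
- An unrounded d of 0.0945 gives 107.5, so 108. The stated figure is reproduced within rounding.
- p = 0.5 maximises p(1 − p), so any other proportion gives a smaller n, further from 108.
- 108 / 0.9 = 120. The dropout step is sound.

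**2. What the formula leaves out.** It gives a total for one undivided sample. After 10% loss each arm has 30 × 0.9 = 27. Even for a proportion, the half-width is then 1.96 × √(0.25/27) = 0.189 in one arm and 1.96 × √(0.5/27) = 0.267 for a difference between two arms. The trial analyses no proportion, so these figures show only that the division into arms was ignored. They do not measure a loss in the planned comparisons.

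**3. What 27 per arm delivers for means.** Two-sample t test, 80% power, two-sided. With baseline adjustment the detectable difference is multiplied by √(1 − r²): 0.714 at r = 0.7, 0.866 at r = 0.5 and 0.600 at r = 0.8.

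| Contrasts (alpha each) | Unadjusted detectable difference (SD) | Power at 0.5 SD, unadjusted | Baseline-adjusted, r = 0.7 (r = 0.5 to 0.8) |
|---|---|---|---|
| One (0.05) | 0.78 | 44% | 0.55 (0.67 to 0.47) |
| Three vs control (0.05/3) | 0.91 | 27% | 0.65 (0.78 to 0.54) |
| All six pairs (0.05/6) | 0.98 | 19% | 0.70 (0.85 to 0.59) |

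For example, 0.777 × 0.714 = 0.55 and 0.906 × 0.714 = 0.65. The Bonferroni rows are illustrations, since the article states only a 0.05 threshold.

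**4. Size needed for a chosen effect.** The article gives no delta or SD, so there is no single corrected total. By the normal approximation, 0.5 SD in one contrast needs 63 per arm unadjusted, 48 with r = 0.5 and 33 with r = 0.7. An effect of 0.8 SD needs 25 per arm unadjusted, which the trial would have.

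**5. The cited study.** 33/120 = 27.5% and 33/108 = 31%. At 20 versus 13, an unadjusted t test has 80% power only for about 1.03 SD.

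**The case against.** The strongest case for the article has four parts.

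- *The arithmetic is right and the gap is disclosed.* Both are true. 108 and 120 reproduce, and the article openly says that sizing for means needed a pilot it could not run. What remains is the basis of the calculation and the conclusion drawn. Disclosing a gap does not support calling the result correct.
- *The single-proportion reading is inferred.* This stands as a caveat: neither p = 0.5 nor an undivided sample is written down. But the stated inputs include nothing about power, effect or groups, so no reading of them yields a between-arm calculation.
- *The comparison may refer to group sizes (20 and 13 against 30) rather than totals.* That would make the wording less odd. It would not make a smaller two-group study evidence for this size.
- *An article may leave detail to a fuller protocol or analysis plan.* That covers omissions. Here the calculation is printed and endorsed.

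A reader might also infer that the trial can detect only large effects. The documents do not support that: evaluation is before and after the programme, and with baseline adjustment a single contrast could detect about 0.55 SD under the assumed correlation. Nor does the article claim or plan equivalence, so a prediction that null head-to-head results will be read as equal effectiveness is speculation. The 0.91 and 0.98 figures depend on Bonferroni; a Dunnett procedure for three contrasts against control would give about 0.88.

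**Conclusion.** Wrong as written. The stated justification concerns a proportion, while the trial compares means or changes among four arms, and the reference to a study of 33 cannot supply what is missing. The calculation therefore supports none of the planned between-arm comparisons.

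A reader might go further and conclude that 120 is too small. That does not follow. Without a target difference and SD, adequacy cannot be judged either way: 27 per arm suffices for effects of about 0.78 SD in one unadjusted contrast, and for smaller ones with baseline adjustment, but falls short of 80% power for 0.5 SD in most of the scenarios examined.

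The attribution of 108 to the single-proportion formula rests on p = 0.5. The adjusted figures rest on the assumed correlation, and all the standardised figures on 10% loss spread evenly over the arms. The conclusion that the stated basis does not fit the planned comparisons depends on none of these.

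**What to change.** Keep 120. Delete the proportion-precision justification and the sentence that calls the calculation correct. Present 120 as a feasibility-based size and state what it delivers, for example:

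> With 27 completers per arm, two-sided alpha 0.05 and 80% power, the detectable standardised between-arm difference is about 0.78 for a single unadjusted contrast (0.91 if Bonferroni-adjusted for three contrasts with control, 0.98 for all six pairs). With baseline adjustment, assuming a pre-post correlation of 0.7 (range 0.5 to 0.8), these become about 0.55 (0.67 to 0.47), 0.65 (0.78 to 0.54) and 0.70 (0.85 to 0.59).

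Report comparisons between exercise programmes with confidence intervals, and note that the size was not set to detect moderate differences between them. The aim of comparing programmes need not change.

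The cost is one rewritten passage. Enrolment, arms and assessments stay as they are, but the trial gives up the claim of a formally validated sample size.
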